## 6.3 Secondary outcomes

The secondary outcomes include:

- a) Migraine days per month (defined as 28 days) week 1 to 4 and week 5 to 8 calculated from the diary of the app.
- b) Headache days and moderate/severe headache days per months (defined as 28 days) after 12 weeks (week 9 to 12), week 1 to 4, and week 5 to 8 will be calculated from the diary of the app.
- c) Migraine specific quality of life measured with the **6-item Headache Impact Text (HIT-6)** over the last 4 weeks. The HIT-6 was designed to provide a global measure of adverse headache impact and was developed to use in screening and monitoring patients with headaches in both clinical practice and clinical research. The HIT-6 is a valid tool for both migraine and chronic migraine.
- d) Self-efficacy is measured with the 6-item short form of the German language adapted **headache management self-efficacy scale (HMSE-G-SF)** over the last 4 weeks. The HSME-G-SF was designed to measure self-efficacy beliefs. The HSME-G-SF is a valid and reliable tool for migraine, chronic tension-type headache, or a combination of 2 or more headache disorders.
- e) Headache attributed burden such as disability and headache attributed lost time is measured with the 5-item **Headache-Attributed Lost Time indices (HALT-30)** over the last 4 weeks.
- f) Migraine-specific health literacy will be evaluated. Because no suitable validated measure is available we will use a self-developed questionnaire with three items. The questionnaire is intended to assess the capability of migraineurs to find, understand, and judge information about the disease and treatment options.
- g) **Drug consumptions** for acute treatment is measured from the medication diary within the app over the last 4 weeks on daily basis.

## 6.4 Further measurements

In addition to the above listed outcomes the following aspects will be measured:

- a) Use of interventions
- b) Safety: Serious Adverse Events, Suspected Adverse Reactions and Serious Suspected Adverse Reactions (for more details see chapter safety).

## 6.5 Mapping of outcomes to DVG categories

In the Digital Healthcare Act (DVG) the concept of positive care effect was introduced. Positive healthcare effects (positive Versorgungseffekte) are defined as either a medical benefit (medizinischer Nutzen) or a patient-relevant improvement of structure and processes (patientenrelevante Struktur- und Verfahrensverbesserungen) in healthcare. The outcomes selected for this study were categorized into one of these two categories (see

Table 2).

**Table 2. Mapping of outcomes according to DVG**

| Outcome                                                | DVG Category                                                               | Notes                                                                                                                                                                                    |
|--------------------------------------------------------|----------------------------------------------------------------------------|------------------------------------------------------------------------------------------------------------------------------------------------------------------------------------------|
| Migraine days (diary)                                  | Medical Benefit - improvement of the state of health                       | Requested by the regulatory body (BfArM) and based on guidelines of the International Headache Society for controlled trials on preventive (pharmacological) treatment.  |
| Headache days (diary)                                  | Medical Benefit - improvement of the state of health                       | Hint from the systematic secondary data analyses of M-sense Active, outcome of many migraine drug studies, e.g. also in AMNOG studies for monoclonal antibodies.                         |
| Migraine specific quality of life - HIT-6              | Medical Benefit – Health-related quality of life                           | Classic outcome of migraine drug & behavioural training studies, assessing migraine specific quality of life.                                                                            |
| Self-efficacy HMSE-G-SF                                | Patient-relevant improvement of structure and processes - Patient Autonomy | Standard measure in the evaluation of behavioral intervention programs in migraine research. Measures whether patients' autonomous health behaviour is improved.                         |
| Disability and headache attributed lost time - HALT-30 | Medical Benefit - Health-related quality of life                           | Adapted and validated version of MIDAS (classic outcome in migraine research) with retrospective focus on 30 instead of 90 days, assessment of burden of disease.                        |
| Migraine-specific health literacy                      | Patient-relevant improvement of structure and processes - Health Literacy  | Self-developed questionnaire                                                                                                                                                             |

## 7 INTERVENTION

### 7.1 Intervention group

M-sense Migräne app consists of the following evidence-based features and interventions. The evidence base has been mentioned in the introduction. Furthermore, it has been described in the systematic evaluation of M-sense Active user data where also the details of the app intervention are described. Here, this list of features and interventions will be provided:

- a) Headache reporting and attack classification diary

- b) Medication intake diary
- c) Trigger factors diary
- d) Analysis function and physician report
- e) Personalized education on disease- and trigger management
- f) Relaxation therapy
- g) Training module
- h) Acute pain therapy
- i) Behavioral Change Techniques

The figure below gives some examples:

[figure not shown]

**Figure 2. Screenshots of the study app**

a) The comprehensive **headache diary** allows a real time tracking of headache occurrences, including headache characteristics, attendant symptoms and experienced pain intensity levels. These headache entries are automatically classified by the M-sense headache classification algorithm, a digitalized version of the ICHD-3-based headache classification. The algorithm allocates single headache attacks to the phenotypes migraine, tension-type headache (TTH), and unclassified headaches. The validity of M-sense's algorithm was assessed by comparing the classification of single headache attacks performed by the algorithm to the attack classification performed by a certified neurologist specialised in headache medicine. The substantial level of agreement between the neurologist and the algorithm was obtained (unweighted kappa=0.74). Most cases of disagreement were due to inadvertent mistakes of the neurologist as identified in the disagreement validity assessment.

b) The **diary for medication intake** allows users to track intake of their prophylactic and acute pain medication and to receive information on proper intake of medications and the potential hazards of medication overuse.

- c) The **diary for trigger factors** list potential migraine trigger factors, e.g. sleep duration, period, alcohol consumption, stress (for details see Wöber & Wöber-Bingöl, 2011). Through descriptive statistics potential individual triggers can be detected.
- d) The **analysis function and physician report** analyses and visualizes the data entered into the app, including headache types, monthly headache occurrence, monthly average pain intensity and frequency of headaches, trigger statistics, headache distribution by time-of-day, day-of-week, and days-in-month and medication intake in weekly and monthly reports, as well as via the in-app calendar. This helps users to self-monitor the course of the disease and their medication intake. The report can be used to facilitate patient-physician communication.
- e) For the **personalized education about disease- and trigger management** the M-sense Migräne app includes 20 individualized knowledge lessons about migraine (e.g. symptoms, trigger factors and causes) and its treatment options (acute and preventive).
- f) For the **relaxation therapy** the app includes several relaxation exercises, such as Progressive Muscle Relaxation, Autogenic Training and Breathing Meditation, with different session lengths. To support behavioral self-management users can set reminders for relaxation therapy.
- g) In the **training module** information on various suitable types of exercise and instructions on how to start practicing them adequately are provided. In addition, the users are supported to set up training plans. To support behavioral self-management users can set reminders for endurance sports.
- h) For **acute pain therapy** M-sense Migräne incorporates non-pharmacological interventions, this includes animated physiotherapy exercises such as self-massage with a focus on migraine-specific pericranial and neck muscular trigger points and stretching exercises, as well as guided visual imagery audio files.
- i) **Behavioral Change Techniques** are used to support intervention engagement and behavioral self-management strategies. A monthly calendar gives an overview of successfully carried out preventive exercises, which prompts self-monitoring. To promote action planning, users can set up weekly plans with reminders for endurance sports and relaxation exercises. Education lessons as well as home-screen messages are personalized by means of diary entries, name, gender and age.

## 7.2 Control group

The control group will gain access to the control study app, an app configuration of the M-sense Migräne app. The control study app will serve as a data input tool and, thus, only include features for study data collection such as a limited headache and medication intake diary and questionnaires. The control study app will serve as a documentation “black box” that will not provide any feedback or interventions about their data entries or behavior. E.g. the user will not be shown the result of headache attack classification

or descriptive statistics about headache patterns. Headache entries can only be seen retrospectively for one week. The documentation within the app assures that both groups have the same way to document outcomes and avoids possible bias by digital placebo effects.

## 7.3 Concomitant treatments

Concomitant treatments are allowed. Existing interventions and the start of new interventions will be documented within the app.

# 8 SAFETY

## 8.1 Risk-benefit assessment

The app M-sense Migräne is a CE marked class I medical device according to Annex IX of the Medical Device Directive (MDD 93/42/EEC) with the conformity assessment route MDD Annex VI. M-sense Migräne will be used within the intended purpose. The app is subject to a risk management process according to ISO 14971. It includes non-pharmacological evidence-based interventions for migraine and is not expected to involve significant risks or burdens for the participants. We expect that the benefits will outweigh the risks. In a previous study within a project funded by the Innovation Fund (SMARTGEM) the intervention was not associated with serious adverse events. M-sense Migräne fulfills the requirements of the Digital Health Applications Ordinance regarding Annex 1 (privacy and data security) as well as Annex 2 (robustness, consumer protection, patient safety, quality of medical content, support of healthcare providers, usability and accessibility, and interoperability). However, misuse of data or a data breach could violate the patient's privacy. These risks are reflected in the manufacturer's privacy impact assessment and mitigation measures are implemented. Each study participant will be informed about the applied interventions as well as about possible risks regarding privacy and data safety prior to study participation.

# 9 ASSESSMENT OF SAFETY

M-sense Migräne is a CE marked medical device with an established risk management which will also take place during the study period.

Safety outcomes defined for the study are the number of participants with serious adverse events, suspected adverse reactions and serious suspected adverse reactions.

All suspected adverse reactions and all serious adverse events will be listed and evaluated. An adverse event is any undesirable experience associated with the use of a therapy in a patient. The event is serious and should be reported when the patient outcome is: results in death or is life-threatening, requires inpatient hospitalization or prolongation of existing hospitalization, results in persistent or significant

disability/incapacity, or results in a congenital anomaly/birth defect (Good-Clinical-Practice-Verordnung, GCP-V).

A suspected adverse reaction in our study is defined as an effect that the app user directly associated (self reported) with the app use. For “serious” the same categories mentioned above are used.

In this study, patients will be asked about suspected adverse reactions and serious adverse events within the app (see Table 3).

In addition, we will collect serious suspected adverse reactions (patients will be informed during informed consent and by the app to call the study office in case they assume to have a serious suspected adverse reactions).

A causality assessment of the serious adverse event with respect to the trial intervention (see Table 3 based on the terms given in the ICH E2A guideline) will be performed. Any event assessed as possibly, probably or definitely related is classified as related to the trial intervention.

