|                                   | health-related quality of life, safety, adherence, migraine-specific health literacy, and headache management self-efficacy of M-sense users.                                                                                                                                                                                                                                                                                                                                                                                                                                                                                                                                                                                                                                                               |
| Study design               | This is a two-armed, open-label, parallel-group, randomized, controlled study. Patients will be randomly allocated to one of the two groups in a 1:1 ratio to gain access either to the full M-sense Migräne app or the Control study app with only data input features. For motivational reasons the control group participants will gain access to the full M-sense Migräne app after 12 weeks. This additional data and the 24-weeks follow-up in the intervention group will not be part of the DiGA-study.                                                                                                                                                                                                                                                                                             |
| Interventions and controls | Intervention group: M-sense Migräne app for 12 weeks.
Control group: Control study app that only includes data input features (as a diary visible for one week without attack classification) and questionnaires. There will be no app interventions and no data will be feedbacked to the patients.                                                                                                                                                                                                                                                                                                                                                                                                                                                                                       |

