**Table 3. Tool for causality assessment of serious adverse events**

| Relationship                                                                            | Description                                                                                                               |
|-----------------------------------------------------------------------------------------|---------------------------------------------------------------------------------------------------------------------------|
| Definitely                                                                              | Temporal relationship
Improvement after dechallenge*
Recurrence after rechallenge
(or other proof of drug cause) |
| Probably                                                                                | Temporal relationship
Improvement after dechallenge
No other cause evident                                          |
| Possibly                                                                                | Temporal relationship
Other cause possible                                                                             |
| Unlikely                                                                                | Any assessable reaction that does not fulfil the above conditions                                                         |
| Not related                                                                             | Causal relationship can be ruled out                                                                                      |
| *Improvement after dechallenge only taken into consideration, if applicable to reaction |                                                                                                                           |

In addition, a severity assessment of the event (mild, moderate or severe) will be performed. Mild means the complication is tolerable, moderate means it interferes with daily activities and severe means it renders daily activities impossible.

Serious adverse event and suspected adverse reaction (patient reported) will be documented in an Serious adverse event log and evaluated by the study team every 3 months.

In case of serious suspected adverse reactions users call the study office and appropriate measures will be taken within 48 hours.

---

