### 6.4 SAFETY MEASUREMENTS

In both groups:

- Number of patients with a serious adverse event during the first 4 weeks, second 4 weeks, and third 4 weeks, and in total.
- Counts of serious adverse events during the first 4 weeks, second 4 weeks, and third 4 weeks, and in total.

In the M-sense Migräne app group only:

- Number of patients with a suspected adverse reaction during the first 4 weeks, second 4 weeks, and third 4 weeks, and in total.
- Counts of suspected adverse reactions during the first 4 weeks, second 4 weeks, and third 4 weeks, and in total.
- Duration of suspected adverse reaction.

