| Number of patients with concomitant activity/activities against headache (all and specific) | daily               | week 1-4, week 5-8, week 9-12                | dichotomous | Yes, no         |                                                                | Chi             | ITT                 |
| Study dropouts                                                                              |                     | week 1-4, week 5-8, and week 9-12, week 1-12 | dichotomous | Yes, no         |                                                                | Chi             | ITT                 |
| Safety measurements                                                                  |                     |                                              |             |                 |                                                                |                             |                     |
| Counts of serious adverse events                                                            | week 4, 8, and 12   | week 1-4, week 5-8, week 9-12                | continuous  | ≥0              | higher values indicate higher number of serious adverse events | Wilcoxon rank test          | ITT                 |
| Number of patients with at least one serious adverse event                                  | week 4, 8, and 12   | week 1-4, week 5-8, week 9-12                | dichotomous | Yes, no         |                                                                | Chi             | ITT                 |

\* with treatment group (fixed factor) and respective baseline value (if applicable) as covariate

**Table 3.** Descriptive outcomes for the group with M-sense Migräne

| Outcomes                                                        | Time of measurement | Refers to...                  | Scale                                    | Possible values | Interpretation                                                        | Analysis method | Analysis population |
|-----------------------------------------------------------------|---------------------|-------------------------------|------------------------------------------|-----------------|-----------------------------------------------------------------------|-----------------|---------------------|

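### Section 9 ties an adverse event to use of a therapy, which conflicts with the plan's own causality scale and its count of serious adverse events in both arms

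*Combined protocol and SAP*

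**What the plan says.** The only definition of an adverse event in either document is in section 9 of the evaluation concept: "An adverse event is any undesirable experience associated with the use of a therapy in a patient". The sentence after it says when such an event is serious, so the SAE inherits the definition. The SAP uses the term SAE without defining it.

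Other parts of the plan treat the SAE more broadly:

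- Section 9 also states: "All suspected adverse reactions and all serious adverse events will be listed and evaluated".
- Section 9 describes collection as follows: "patients will be asked about suspected adverse reactions and serious adverse events within the app". It points to protocol Table 3 at this place, but that table is the causality tool and contains no question text.
- The Synopsis (Safety row) has SAE information collected at 4, 8 and 12 weeks and has the investigators assess any relationship to the interventions from those data.
- Protocol Table 3 grades SAEs down to *Not related*, described as "Causal relationship can be ruled out".
- SAP 6.4 lists, for both groups, "Number of patients with a serious adverse event during the first 4 weeks, second 4 weeks, and third 4 weeks, and in total". Suspected adverse reactions come under a separate restriction: "In the M-sense Migräne app group only".
- SAP 10.7 compares groups by chi-square or Wilcoxon test, and SAP Table 2 has a row for "Number of patients with at least one serious adverse event".

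Of the control app the Synopsis says: "There will be no app interventions and no data will be feedbacked to the patients".

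**The concern.** A between-arm comparison of SAEs needs an SAE to mean the same thing in both arms, and that meaning should not depend on exposure. Section 9 puts a link with therapy inside the definition. The plan already deals with that link in two other places: the suspected adverse reaction, which the user attributes to the app, and the causality grading. The definition therefore merges two ideas that the rest of the plan keeps apart.

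The wording matters more than usual here. SAEs are self-reported in the app by patients who know their allocation, and SAEs are the only adverse-event measure that SAP 6.4 sets for both arms. Because the question is not given, the definition is the only documented basis for writing it and for deciding what enters the SAE log. If the link with therapy were carried into the question, a control patient would have less to attribute an event to. If it were applied evenly, unrelated SAEs would be undercounted in both arms.

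**Working it through.** **Step 1. Set the provisions side by side.** Consider a hospital admission after an accident, unconnected with any treatment.

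| Provision | Does the event count? |
|---|---|
| Section 9, definition read literally | No, in either arm |
| Section 9, listing of SAEs | Yes, if it is an SAE; all are listed |
| Synopsis, Safety row | Yes; relationship is judged after collection |
| Protocol Table 3 | Yes; graded *Not related* |
| SAP 6.4, 10.7 and Table 2 | Yes, in both arms |

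Only the definition excludes it. *Unlikely* and *Not related* have little to apply to if an event must already be linked with a therapy in order to exist.

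Now consider an admission of uncertain cause. In the app arm there is a study intervention to which it may be linked. In the control arm there is none, so any link must be with some other treatment. A literal reading could then count fewer control events.

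**Step 2. Inputs for an illustration.** The documents give 173 per group and a two-sided 0.05 level. The 173 reproduces. The normal approximation gives 2 × (1.960 + 0.842)² × (4.20/1.27)² = 171.7, rounded up to 172, and the t-test calculation gives 172.65, rounded up to 173. That figure was set for migraine days; it is used here only as the arm size. The documents give no SAE risk and no capture fraction. Both are assumptions below.

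**Step 3. How few events decide the test.** With *a* affected patients in the app arm, none in control and N = 346, the uncorrected chi-square is N·a/(N − a).

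- a = 3: 346 × 3/343 = 3.03, below 3.84.
- a = 4: 346 × 4/342 = 4.05, above 3.84.

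Four against none is enough.

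**Step 4. Probability of a false excess in the app arm.** Assume the same true risk p in both arms, full capture in the app arm and a fraction f captured in control. Affected patients are Binomial(173, p) and Binomial(173, p·f). Summing over all outcomes with chi-square above 3.84 and more events in the app arm gives:

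| Assumed risk p | f = 1 | f = 0.5 | f = 0 (extreme bound) |
|---|---|---|---|
| 1% | 1.8% | 4.1% | 9.7% |
| 2% | 2.3% | 10.1% | 45.6% |
| 3% | 2.3% | 13.6% | 76.5% |

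**Step 5. Match the period to the planned test.** SAP Table 2 refers the SAE tests to three 4-week windows; the 12-week total appears in SAP 6.4. A 12-week risk of 3% spread evenly is about 3%/3 = 1% per window. The 1% row then applies to each window: 4.1% if half of control events are missed, and 9.7% at the bound.

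**The case against.** The strongest reply is that the plan never uses the sentence as a filter. Section 9 lists all SAEs, the Synopsis judges relatedness afterwards, SAP 6.4 counts SAEs in both groups, and Table 3 grades unrelated ones. On this view Table 3 shows the intention, and the definition is merely loose. As to intention, that is probably right. But no other definition exists, and nothing tells the person writing the question or keeping the log to disregard this one.

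A reader might go further and infer that the SAE comparison screens events by their link with the app, so that control events are removed by construction and the app is made to look harmful. The documents do not support that, for three reasons:

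- The text says a therapy, not the app. Section 7.3 allows concomitant treatments in both arms, so a control event can meet the definition. Where the authors mean the app or the trial intervention, as for the suspected adverse reaction and the causality grading, they say so.
- No screening step is described. Patients report through the app, and the question wording that would have to differ between arms is not given.
- The f = 0 column assumes total loss in one arm and none in the other, which contradicts the both-group counting. It is a bound and not a forecast.

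The consequence is also limited. SAP 9.1 makes all tests other than the primary explorative, and SAP 10.7 also tabulates withdrawals for safety concerns, so SAEs are not the whole safety picture.

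**Conclusion.** The inconsistency is real. The definition in section 9, on which the SAE rests, conflicts with the listing of all SAEs, with the lower grades of protocol Table 3 and with the both-arm comparison in the SAP. Applied literally, it omits SAEs unconnected with any therapy and could count fewer events in the control arm. Whether capture would in fact differ between arms can be neither confirmed nor excluded from the documents.

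The size is therefore conditional. At assumed risks of 1% to 3%, missing half of control SAEs raises the chance of a false app-arm excess from about 2% to between 4.1% and 13.6%. These values rest on equal true risk, full capture in the app arm and an uncorrected chi-square test over a period that carries the stated risk. The primary analysis is unaffected. The point deserves correction because the definition underlies the plan's main adverse-event contrast between randomised arms and is easy to repair.

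**What to change.** Reconcile section 9 with protocol Table 3 and SAP 6.4:

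- Define an adverse event as any untoward medical occurrence in a randomised participant, in either arm, whether or not it is considered related to the app.
- Leave relatedness entirely to the causality assessment and to the suspected adverse reaction.
- Refer to this definition in SAP 6.4, since the SAP has none of its own.
- Confirm that both app versions show the same SAE question at weeks 4, 8 and 12, without reference to therapy or app use. Give its wording in section 9, where the pointer now leads to the causality table.

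The cost is one sentence, a cross-reference and a check of the question text. The downside is a few more unrelated events to log and grade. The analysis methods and sample size do not change.
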